#### **2.4.2 Secondary Endpoint:**

- To evaluate changes of the treated IVD induced by regenerative therapy by quantitative Magnetic Resonance Imaging (MRI) signal measurements in T2, T1spin/echo, and T1rho weighted images that allow a quantitative measure of the NP extracellular matrix.
- To evaluate modification of disability (ODI) and quality of life (SF-36 scores) considered as continuous measures, between baseline and 1, 3, 6, 12 and 24 months.
- Safety and tolerability will be evaluated by recording adverse events (AEs) and serious AEs (SAEs) throughout the study till 24 months. Number of participants with adverse events, the correlation of the AE to the IMP and their severity will be used as a measure of safety and tolerability.
- To evaluate consumption of medications to relieve pain such as type and dose of analgesics will be evaluated. Paracetamol (acetaminophen) and levels 2 analgesics will be assessed throughout the study at each visit.

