#### Adverse drug reaction (ADR)

All noxious and unintended responses to a medicinal product related to any dose should be considered adverse drug reactions.

An adverse reaction is an AE that is at least possibly related to the administration of the study medication or procedure. When assessing the relationship ("related" or "unrelated") between an AE and the study medication or procedure, the following points should be taken into consideration:

- close timely relationship between administration of study medication or procedure and occurrence of AE
- information about the side effect profile of the study medication or procedure from non-clinical and clinical studies
- mechanism of action of study medication or procedure potentially explaining the occurrence of the AE
- other factors with causal potential
- impact of concurrent therapeutic or diagnostic measures
- personal physical or psychological stress factors on the participant's side

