### Expected Adverse Reaction related to injection of autologous bone marrow mesenchymal cell (undetermined frequency, not severe except for immunological reaction)

- transient lumbar pain
- elevation of the body temperature (>37,5°C)

- shivering
- pruritus

*Expected Adverse Reaction related to local intra-discal injection*

- headache and nausea (undetermined frequency, not severe) The following adverse reactions are severe but rare
- local infection (discitis),
- reherniation in operated segments,
- exacerbation of pain, back pain, ischialgia, sciatica, pain in extremity,
- facet joint syndrome,
- meningitis,
- epidural abscess,
- arachnoiditis,
- intrathecal hematoma,
- retroperitoneal hematoma,
- cauda equina syndrome,
- acute disc herniation,
- paralysis,
- cerebrospinal fluid leak.

*Expected Adverse Reaction related to the concomitant medication*

Cf. the current Summary of Product Characteristics (SmPC) to the product.

*Expected Adverse Reaction related to MRI*

Panic attack

*Expected Adverse Reaction related to local  
anesthesia*

- Related to local anesthetic or antiseptic :

Cf. the current Summary of Product Characteristics (SmPC) to the product (1% xylocain for local anesthetic, and chlorhexidine for antiseptic)

- Related to the procedure/technique of local anesthesia:

Anesthesia failures and insufficiencies

Hematomas and arterial dissections

Infections

Neurological lesions (traumatic nerve location or intraneural injection or injected solution toxic)

Error on injected product (Ex: antiseptic, physiological saline)

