#### **8.5 Investigator responsibilities**

##### AEs

Complete and appropriate data on all AEs (only clinically significant event or value) experienced during the clinical trial should be recorded on the AE form of the CRF on an ongoing basis for the duration of the study. Each AE report shall include a description of the event, an assessment of its seriousness according to the criteria listed above, its duration, intensity, relationship to the study medication, other causality factors (if any), any concomitant medication dispensed, actions taken with the study drug or other therapeutic interventions and outcome at the end of the observation period.

The adverse events will be encoded and graded according to CTCAE Criteria Grade 1-5

(Common Terminology Criteria for Adverse Events). A copy of the CTCAE Version 5.0 can be downloaded from the CTEP homepage (<http://ctep.info.nih.gov>). If there is no CTCAE grading possible, the intensity of the adverse event has to be classified in categories:

- Mild (Grade 1) – transient or minimal symptoms; no change in activity or need of medication
- Moderate (Grade 2) – symptomatic; moderate change in activity; no reduction in social activities

- Severe (Grade 3) – incapacitating; bed rest required; loss of work; reduction in social activities
- Life threatening (Grade 4) – significant clinical intervention or hospitalization required
- Fatal (Grade 5)

For each AE, a separate AE form will be filled in.

Follow up of AEs: AEs will be followed until their resolution or stabilisation. However, the observation period will be cut off after the last patient has finished his final visit (LPLV). During monitoring visits, the study monitor will assess accuracy and completeness of all AE forms generated since the last visit by 100% source data verification. Cases of AEs reported earlier for which the outcome is still pending will be checked for new data and developments. Furthermore, queries on AEs reported earlier will be solved with the Investigator. AEs will be reported in the final study report.

The sponsor must be informed immediately of the occurrence of any AE grade 3-4-5 by the associated centre.

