## 8.6 Sponsor responsibilities

### Serious Adverse Event and new event

The relation between the event and the study drugs should be evaluated by the sponsor. The sponsor will evaluate whether the events are expected or unexpected.

The sponsor will report any SUSAR and new events according to the legislation and good clinical practice. Any Serious Adverse Reaction related to injection of allogeneic bone marrow mesenchymal cell, to graft rejection of allogeneic bone marrow mesenchymal cell, to local intra-discal injection and those related to bone marrow donation will be declared to the corresponding national competent authority in the same way that SUSARs Regulatory declaration is made within a maximum of:

- without delay for serious adverse unexpected fatal or life-threatening. In this case, additional relevant information should be sought and passed within a further period of 8 days.
- 15 calendar days for all other serious unintended effects. The same additional relevant information should be sought and transmitted in a further period of 8 days.

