### Assessment of Adverse Events

The assessment of the relationship of an AE to the administration of Drug Product is a clinical decision based on all available information at the time of, and after the occurrence of the event. The factors to be considered when evaluating the relationship of an AE to the Drug Product include:

- Temporal sequence from drug administration: the event must occur after the Drug Product is given. The length of time from exposure to medication to event should be evaluated in the clinical context of the event.
- Recovery on discontinuation (dechallenge), recurrence on reintroduction (rechallenge).

- Underlying, concomitant, intercurrent diseases: each report should be evaluated in the context of the natural history and course of the disease being treated and any other diseases the patient may have had prior to, or developed during the course of the study.
- Concomitant medication or treatment: the other drugs the patient is taking or the treatment the patient is receiving at the time of the event should be examined to determine whether any of them may be recognized to cause the event in question.
- Known response pattern for this class of drug.
- Exposure to physical and/or mental stress: the exposure to stress may induce adverse changes in the patient and may provide a logical explanation for the event.
- The pharmacology and pharmacokinetics of the Drug Product: absorption, distribution, metabolism and excretion of the Drug Product or other medications the patient is receiving, coupled with the pharmacodynamic responses, should be considered when evaluating an event. From a statistical and regulatory point of view, an AE will be categorized as “reasonable” or “not reasonable” related to Drug Product.

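### AE causality is judged against the product in some sections and against product or procedure in others, so a marrow-harvest event cannot be classed as related under section 8.6

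*Protocol*

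**What the plan says.** The protocol states in several places what an adverse event is to be judged against, and the places differ.

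These name the product alone:
- Section 2.4.2, the safety endpoint: "Number of participants with adverse events, the correlation of the AE to the IMP and their severity will be used as a measure of safety".
- Section 8.5, among the contents of each AE report: "its duration, intensity, relationship to the study medication". The same list then allows for other causal factors, if there are any.
- Section 8.6, Serious Adverse Event and new event: "The relation between the event and the study drugs should be evaluated by the sponsor".
- Section 8.6, Assessment of Adverse Events: "The assessment of the relationship of an AE to the administration of Drug Product is a clinical decision". The category kept for statistical and regulatory purposes is whether a relation to the Drug Product is reasonable. One listed factor is that the event has to come later than the Drug Product.
- Section 8.2, the SUSAR definition: causality is to the study medication. The procedure appears only in the part about whether the event is listed.

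These name the product or the procedure:
- Section 8.2, Adverse drug reaction: "An adverse reaction is an AE that is at least possibly related to the administration of the study medication or procedure".
- Section 8.2, the SAR and SESAR definitions.

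Section 8.3 gives the injection its own list, headed "Expected Adverse Reaction related to local intra-discal injection", apart from the list for the cells. Section 8.6 also has serious reactions to the intradiscal injection and to marrow donation declared in the same way as SUSARs.

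**The concern.** The treatment strategy under test consists of a marrow harvest, a disc puncture and the cells. If relatedness means relation to the product in one section and to product or procedure in another, the same event can be a reaction by definition and unrelated in the endpoint. Section 2.4.2 makes relatedness one of the safety measures, so its meaning should not depend on which section the assessor last read.

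The conflict also reaches data capture. Section 8.5 fixes what the AE report holds, and an attribution to a procedure is not asked for explicitly. An analysis plan written later cannot reliably recover an attribution that was not collected.

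**Working it through.** No arithmetic beyond the visit days applies, and the plan gives no figure to reproduce. The check sets the rules side by side and applies each to two events: one arising at the harvest and one arising from the disc puncture.

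| Place | Judged against | Event at the harvest | Event from the disc puncture |
|---|---|---|---|
| 2.4.2 endpoint | IMP | unrelated if read literally | ambiguous |
| 8.2 adverse reaction | medication or procedure | reaction | reaction |
| 8.2 SAR, SESAR | medication or procedure | meets the causality test | meets the causality test |
| 8.2 SUSAR | study medication | fails the causality test if read literally | ambiguous |
| 8.5 AE report | study medication, then other causal factors | procedure not asked for explicitly | ambiguous |
| 8.6 sponsor evaluation | study drugs | procedure not named | ambiguous |
| 8.6 assessment | giving of Drug Product, event after it | cannot be related | may be related |

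**Harvest**
1. The schedule in section 6.1 puts the marrow withdrawal at Day -45 to Day -31 and the treatment at Day 0.
2. The gap from harvest to product is therefore 0 - (-31) = 31 days at the shortest and 0 - (-45) = 45 days at the longest.
3. Section 8.6 requires the event to follow the Drug Product. An event arising at the harvest comes before it, so it cannot be classed as related there.
4. Section 8.2 judges closeness in time from the medication or the procedure. The same event can be an adverse reaction there.
5. The two sections cannot both be applied to that event.

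**Disc puncture**
1. Section 8.2 counts a puncture harm as a reaction, and 8.3 lists such harms as expected reactions to the injection.
2. The assessment part of 8.6 speaks of administering the product. In this trial that is the intradiscal injection (5.5), so a puncture harm can be judged related.
3. Sections 2.4.2 and 8.5 speak of the IMP or study medication and can be read to leave the needle out.
4. Different assessors can therefore classify the same event differently.

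**Serious reactions**
1. The declaration duty in 8.6 needs to know which serious events are due to the injection and which to the marrow procedure. The report in 8.5 does not explicitly ask.
2. Under 8.2 a serious, unlisted event caused only by a procedure is a SAR. Read literally, it is neither a SESAR, because it is unlisted, nor a SUSAR, because it is not related to the medication.

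**The case against.** The strongest reply is that little is lost.

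- Section 7.3 tabulates all AEs by treatment group whatever their cause, and section 8 measures safety by number, type and distribution between arms with no relatedness filter. Section 6.2.4 has AEs recorded before discharge from the harvest. This stands: harms do not vanish from the safety results.
- Section 8.6 has serious reactions to the injection and to marrow donation declared like SUSARs, and its expedited-reporting list includes SAEs that may be linked to trial procedures. This also stands, so the sponsor section is not confined to the cells.
- The report in 8.5 has room for other causal factors, and the eCRF itself is not shown. This stands in part: a procedural cause can be written in, but it is not a required attribution.
- The temporal rule is one factor in a list. That is so, but it is worded as a condition.

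Three stronger readings are tempting.

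1. A reader might infer that most severe harms would be counted as unrelated. Section 8.3 has 4 reactions under the cells and 14 bullets under the injection, 13 of them headed severe but rare. Those counts are of list entries, not events. The only frequency given is for discitis, below 0.1% (1.4, 5.8), and the inference also requires relation to the product to exclude its injection.
2. A reader might infer a biased comparison between arms, because sham patients receive no product. The assessing investigator is blinded (3.3, 8.4), this arises in any blinded sham trial, and the protocol specifies no between-arm test of related events.
3. A reader might infer that 8.2 is uniform and only the other sections stray from it. The SUSAR definition shows otherwise.

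**Conclusion.** The contradiction stands and should be corrected. Its reach is limited to the relatedness measure named in 2.4.2 and the classification of reactions in 8.2, 8.5 and 8.6. It is definite for events arising at the harvest, which the 8.6 assessment rule can never class as related. It is an ambiguity, not an error, for the disc puncture. All-cause counts by arm are unaffected.

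No number of misclassified events can be given, because the documents state no rate for harvest or puncture events in this design.

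The conclusion rests on three assumptions:
- The temporal rule in 8.6 is applied as worded.
- Harvest events are collected as the text of 6.2.4 says, although the AE row of the schedule in 6.1 is marked only from Day 0.
- Marrow donation in 8.6 means the patient's own harvest. That sentence also speaks of allogeneic cells, while this trial uses autologous ones.

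**What to change.** - Use one causality reference, the study medication or procedure, in 2.4.2, the SUSAR definition in 8.2, the AE report in 8.5, and both the evaluation and the assessment parts of 8.6.
- On the AE form, in both arms, record relatedness to the product and, separately, to trial procedures: harvest or sham harvest, injection or sham puncture, and sedation or anaesthesia.
- Reconcile the temporal rule in 8.6 with events that arise at the harvest, before any product is given.
- Tabulate related AEs by arm on that basis, next to the all-cause tables of 7.3.

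The cost is one extra eCRF field and one table. The reported related-AE rate may come out slightly higher, because procedural events would then count. Sample size and the efficacy analysis do not change.

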### **1.7 Risk minimisation plan:**

The sham treatment in the control arm is not harmful to the patient: no disc injection, no placebo injection will be performed in the control patients. The patients with IDD are chronic patients, painful but with no vital risk or no significant risk of delaying effective therapy. The 6 months follow up with conventional therapy is not a reduction of chance to IDD cure as it is a slow irreversible disc degeneration.. Conventional treatment as physiotherapy or analgesic is allowed during the trial period (NSAID and opioid as suggested by “standard of care” [Cartabellotta et al., 2017]). In case patients became painful and who develop “peripheral neurological deficit” they will undergo electromyography of the legs. In case the results obtained show pinched sciatic nerve, the investigator will decide to exclude the patients from

clinical trial and shift the patient to the appropriate standard of care (NSAID, steroid injection, rest, physiotherapy)[Cartabellotta et al., 2017]. In case of severe neuropathic pain (sciatica), the patient will be allowed to perform surgery, he will be considered as a failure. We enclose adequate risk minimization measures in the protocol avoiding the inclusion of patients who are not eligible to the intravertebral disc surgery or so painful that they have high probability to undergo surgery in the next 6 months period as well as patients with herniated discs.

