## **Pain**

The measurement of pain will be determined by self-report of current pain in rest and in motion in the low back pain using a VAS scale. In brief, the VAS consisted of a 10 cm horizontal line anchored with descriptors of pain including "no pain" on one end (left) and "extreme pain" on the other (right). After sitting for 10 minutes, subjects struck a vertical line through the 10 cm VAS representing their CP, and the distance from left end (no pain) to the vertical line was recorded in centimetres. In addition, the patients will fill VAS tests indicating the amount of pain experienced at rest, and in motion.

The drug consumption of painkillers will be assessed throughout the study at each visit. A diary file containing doses, drug name and indication will be given to each patient. The investigator will control this book at each visit. A reduction in dose or frequency of administration of painkillers is an indirect marker of the benefits of MSC therapy.

**Employment and work status** will be assessed. For this we will assign each of the patients to one of 4 categories designated as "employable" which included those who were unemployed due to pain, employed but on sick leave, laid off, or working. The other categories include retired, disabled, and elderly at least 60 years of age, eligible for social security.

**Structural assessment:** Evolution of affected disc(s) by quantitative Magnetic Resonance Imaging (MRI) density measurements in T2 and T1spin/echo and T1rho weighted images performed at 0, 6 12 and 24 months used as an indication of disc fluid and GAG content. The "quality" of the patient's lumbar disc will be monitored non invasively using T2weighted MRI sagittal images (Orozco et al., 2011) and, in T1spin/echo MRI. Lumbar disc grading will be performed in the sagittal T2 weighted images by two physicians independently who were experienced in MRI of the spine. They will review each intervertebral disc from L1–2 to L5-S1 by the modified Pfirrmann criteria. The modified Pfirrmann grading system assesses degenerated intervertebral discs by MRI for the asymmetry in disc structure, distinction of the nucleus and the annulus, signal intensity of intervertebral discs and height of intervertebral discs and assigns grade 1 to 8 for disc degeneration (Table by Griffin et al. Spine 2007).

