### **5.7 Post-treatment care**

The patient is discharged after an observation period of 2 hours. Walk for moderate periods is authorized. Labor activity is suspended for one week. The pain medication is tailored to the needs of each patient and the use of NSAIDs should be avoided. The longterm monitoring will consist of out-patient visits and MRI.

The patients are followed for 2 years on clinical examination, spine MRI. For 2 years they will be followed annually on clinical basis to assess any unexpected long term side effect.

In case the patient have not responded after end of study (3 years) or relapse, he may be eligible for cell therapy when the product will be available on routine basis, or benefit for treatment recommended by EULAR (physiotherapy, steroid or surgery)

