| Checking inclusion and exclusion criteria                           |                | X           |                             |                  |                       |                       |            |             |              |              |
| Randomization                                                       |                |             | X                           |                  |                       |                       |            |             |              |              |
| Pain lumbar spine (VAS), ODI, SF-36                                 | X              | X           |                             | X                | X                     | X                     | X          | X           | X            | X            |
| Lateral MRI, T2, quantitative                                       | X d |             |                             |                  | X                     |                       |            | X           | X            | X            |
| Adverse Events                                                      |                |             |                             |                  | X                     | X                     | X          | X           | X            | X            |
| Concomitant medication                                              |                | X           |                             | X                | X                     | X                     | X          | X           | X            | X            |

a: NSAIDs washout of at least 2 days before screening, inclusion and baseline. NSAIDs will not be authorized during the first 6-month after baseline. However, if needed after the first 6 months, NSAIDs could be used

b: Patients will be required to refrain from taking paracetamol or opioids within 24 hours of each clinical visit for efficacy evaluations

c: vital signs: Temperature, heart rate, arterial blood pressure, height, weight

d: MRI was also used to assess the Pfirrmann and Griffith's score

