#### **6.2.10 Visit 5: Month 24**

- Vital signs
- Physical exploration
- Blood sampling for routine laboratory testing
- Urinalysis
- Lateral MRI, T2, quantitative
- Pain assessment of the lumbar spine by visual pain scale (VAS)
- Oswestry Disability Index in order to measure a patient's permanent functional disability, Quality of life assessment using SF-36
- Adverse event assessment
- Concomitant medication
- Instruction for wash out (NSAIDS washout of at least 2 days before this Visit, no painkillers 24h before the visit)
- Prohibition of NSAIDsa

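### The analgesic-consumption endpoint does not name NSAIDs, although they become usable after month 6, and the NSAID rule is stated inconsistently

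*Protocol*

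**What the plan says.** The objective in 2.3.2 is consumption of pain-relieving medication by type and dose. Section 2.4.2 repeats this in broad terms ("To evaluate consumption of medications to relieve pain such as type and dose of analgesics will be evaluated") and in the next sentence becomes specific: "Paracetamol (acetaminophen) and levels 2 analgesics will be assessed throughout the study at each visit". Section 4.2, under Pain, gives the direction of interpretation: "A reduction in dose or frequency of administration of painkillers is an indirect marker of the benefits of MSC therapy".

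The protocol refers to NSAID use in several places:

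- Section 1.7: "Conventional treatment as physiotherapy or analgesic is allowed during the trial period (NSAID and opioid as suggested by" the standard of care that it cites. No time limit is given.
- Section 5.7, on care after the procedure: "the use of NSAIDs should be avoided". No end date is given.
- Section 6.4: NSAIDs are barred for the first six months of the study and may be used afterwards if needed.
- Section 6.1, footnote a: the same six-month bar, counted from baseline, followed by "However, if needed after the first 6 months, NSAIDs could be used".
- Section 6.1, schedule row, and the visit lists: a prohibition is marked at every visit from V0 to month 24. At months 12 and 24 the lists (6.2.9 and 6.2.10) read "Prohibition of NSAIDsa", where the final letter is the mark of footnote a.

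**The concern.** An endpoint on analgesic consumption should count every analgesic class that patients may take. Otherwise a change of class looks like a change in need. Here the specific sentence of the endpoint leaves out a class that the protocol makes available for most of follow-up. Because NSAIDs may be taken after month 6 if needed, their use depends on symptoms. Omitting them is then unlikely to be neutral between the arms: the arm with more residual pain could show lower use of the drugs that are counted.

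The second problem concerns conduct as well as analysis. If site staff cannot tell from the protocol when NSAIDs are allowed, use will vary for reasons unrelated to treatment, and consumption becomes harder to interpret whichever drugs are counted.

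**Working it through.** No figure in the plan has to be reproduced, so the check consists of setting the passages side by side.

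**How long NSAIDs are usable but unnamed.** Follow-up is 24 months (2.1). The bar lasts 6 months (6.4; 6.1 footnote a). 24 − 6 = 18 months, and 18/24 = 75% of follow-up. Of the five post-treatment visits (months 1, 3, 6, 12 and 24), the last two fall in this period.

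**Whether the word painkillers includes NSAIDs.** The inclusion criteria (3.1) list an NSAID washout of 2 days and a painkiller washout of 24 hours as separate items. The schedule in 6.1 gives them separate rows and separate footnotes. The footnote to the painkiller row reads "Patients will be required to refrain from taking paracetamol or opioids within 24 hours of each clinical visit for efficacy evaluations", so it covers paracetamol and opioids. The visit lists in 6.2 keep the same split. Section 4.2 describes rescue medication as paracetamol and then tramadol, without NSAIDs. This usage suggests that the reduction in painkillers which 4.2 treats as a marker of benefit concerns paracetamol and opioids.

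**What follows if the named list is used.** Take a hypothetical patient on paracetamol and tramadol at month 6 who replaces both with an NSAID at month 7. On the named list (reading level 2 as including tramadol), consumption at months 12 and 24 is nil. On a list that includes NSAIDs, the patient has changed class and has not stopped. The direction of the error is clear. Its frequency is not, because the documents give no rate of switching.

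**Whether the data exist.** The diary in 4.2 records dose, drug name and indication. The diary in 6.4 covers medication use generally. Concomitant medication is recorded at every visit from V0 to V5 (6.1). NSAID intake after treatment is therefore captured. The gap is in the definition of the endpoint, not in data collection.

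**Whether the NSAID statements agree.**

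| Place | NSAIDs in months 0-6 | NSAIDs after month 6 |
|---|---|---|
| 1.7 | allowed, no limit stated | allowed |
| 5.7 | to be avoided | no end date stated |
| 6.4 | barred, counted from the study | usable if needed |
| 6.1 footnote a | barred, counted from baseline | usable if needed |
| 6.1 row, 6.2.9, 6.2.10 | marked as prohibited | marked as prohibited, with a mark to footnote a |

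Section 1.7 conflicts directly with 6.4 and footnote a for the first six months. Sections 6.4 and 6.1 also start the clock differently. If the study is taken to begin at screening (Day −45 to −41 in 6.1), which is an assumption, the two six-month periods end 41 to 45 days apart.

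**The case against.** A reader might infer that NSAIDs are shut out of the endpoint, so that a patient who switches is recorded as using no analgesic at all. The documents do not support that. The first sentence of the endpoint is broad, the second does not say that its list is exhaustive, no passage excludes NSAIDs, and their use is recorded. The protocol also gives no formula for combining or scoring consumption; that may properly be left to the SAP. All of this stands, and it limits the point to an endpoint that is ambiguous and incompletely specified. It does not remove the point: recording a drug does not put it into an endpoint, and the protocol itself chose to name the drugs assessed.

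A reader might also infer a flat contradiction between the prohibition listed at months 12 and 24 and the permission in footnote a. The entries carry the mark of that footnote, which largely explains them. What remains is a lack of clarity: a row headed as a prohibition is ticked at visits where its own footnote allows use. The NSAID washout listed at those visits does not settle the matter, because it is also listed at months 1, 3 and 6.

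The sentence in 5.7 follows instructions for the hours and the week after the procedure, so it may be meant as short-term advice, although it does not say so. The conflict between 1.7 and 6.4 with footnote a has no such explanation.

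**Conclusion.** The point holds as one of definition and consistency on a secondary endpoint. Section 2.4.2 names paracetamol and level 2 analgesics and leaves NSAIDs unnamed, while the protocol allows NSAIDs for 18 of 24 follow-up months. Given the protocol's separate use of the two terms and the interpretation in 4.2, an analysis that follows the named list could read a move to NSAIDs as benefit. This rests on two assumptions: that the analysis follows the list rather than the broad sentence before it, and that some patients do switch. No size for the resulting bias can be given from the documents, and nothing in them shows that NSAIDs would be the analgesic most used after month 6.

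Separately, the NSAID statements do not agree. The clearest conflict is 1.7 against 6.4 and footnote a. The different starting points, the open-ended wording of 5.7 and the prohibition row at months 12 and 24 add to it.

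**What to change.** In 2.4.2 and 4.2, name NSAIDs explicitly among the analgesics assessed, and use the same list wherever a reduction in consumption is interpreted. Take the data from the diary and the concomitant-medication records already planned. Report consumption by class and by arm, separately for months 0-6 and 6-24, because the drugs available change at that boundary under 6.4 and footnote a and a single figure over 24 months would mix the two periods. If reconciling the rule moves the boundary, move the split with it.

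Reconcile the NSAID statements in 1.7, 5.7, 6.1 (row and footnote a), 6.2.9, 6.2.10 and 6.4, including the date from which the six months are counted. Which rule should apply is for the sponsor and the investigators to decide.

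The cost is a wording change to one secondary endpoint, slightly more tabulation, and a clarifying amendment for the NSAID passages. No new data are needed. If the classes are to be combined into one measure, a common dose metric has to be chosen in advance; reporting by class avoids that.
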